#### Electroencephalography

The brain activities will be recorded using a 64-channel EEG system (EB Neuro, Italy) with a sampling rate of 1024 Hz and bandwidth of 0.2–70 Hz. The Ag/Ag Cl surface electrodes with a diameter of 8 mm and an impedance of less than 20 kHz, will be distributed throughout the whole head of the participants. The 21 electrodes, according to the international 10/20 system, will be placed in Fp1, Fpz, Fp2, F7, F3, Fz, F4, F8, T3, C3, Cz, C4, T4, T5, P3, Pz, P4, T6, O1, Oz, O2. A reference and ground electrode will be placed on the mastoid process and the wrist of the right hand respectively. To record vertical and horizontal eye movement, a pair of electrodes will be placed above and below the right eye and a pair of electrodes will be placed at the corner of each eye. Blinking and eye movement artifacts will be monitored with the electrooculogram and the O1 and O2 electrodes. The EEG will be recorded for 3 min under two conditions: while subjects will rest with their eyes open and while they will be typing, during the first and last 3 min of continuous typing. Thereafter, raw EEG data will be imported into LORETA version 2015–12-22 to extract the frequency domains (i.e., Fast Fourier transform, FFT) for delta, theta, alpha, beta, and gamma rhythms, by 1024 sampling frequency and two epochs (2048) for 21 electrodes. Then the relative power levels of each band will be calculated.

### Participant timeline {13}

The study will be performed between October of 2022 and March of 2023. The details of the schedule of enrollment, interventions, and assessments (according to the SPIRIT) are shown in Fig. 2.

**Fig. 2 Fig2:**
[figure not shown]
The schedule of study enrollment, interventions, and assessments (according to SPIRIT)

### Sample size {14}

Based on pilot data of 12 subjects (i.e., 6 cases for slump posture and 6 cases for normal posture), the sample size was calculated using G*Power 3.1.9.4 (Düsseldorf, Germany) software. Sample size estimation was conducted according to one-tailed testing with an alpha set at 0.05 and the desired power of 0.90. For the first part of the study, a sample size of 50 participants distributed in two groups was estimated. For the second part, we calculated that 30 subjects with slump posture, are needed.

To consider a potential 20% drop-out rate, the sample size is 72 participants (36 in each group).

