### Trial design {8}

This is a single-center, assessor-blinded study with two parts; the first part is exploratory research with 1:1 allocation, designed to compare the outcome measures between the normal and slump posture individuals, and the second part is a crossover randomized controlled trial with a superiority design which aims to compare the effects of tDCS and stretching exercises to improve the outcome measures of the study. The study will be performed between October of 2022 and March of 2023. All the outcome measurements will be assessed during the first (T1) and last (T2) 3 min of typing. Figure 1 shows the slump posture group flowchart.

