## Statistical methods

### Statistical methods for primary and secondary outcomes {20a}

Data analysis will be performed using SPSS, version 22 (IBM, NY, USA). Baseline characteristics such as age, weight, height, BMI, years of computer use, and daily computer usage will be summarized with standard descriptive statistics. Depended variables will be described with means and standard deviations. The normality of distribution will be checked by Kolmogorov–Smirnov.

Multivariate ANOVA (MANOVA) will be used to compare the variables between correct and slump posture groups.

Statistical analysis of the outcomes of 3 conditions in the slump posture group will be conducted using repeated measures ANOVA and LSD (least significant difference) post hoc test. The significance level of tests will be considered at 0.05. Mean difference and standardized mean difference and their 95% confidence intervals (Cohen’s D) will be calculated as effect sizes.

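### The 0.90 power claim does not match the planned tests or the stated drop-out, mainly for the crossover part: sizing is one-tailed, the tests are non-directional, and 36 less 20% leaves 28.8, not 30

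*Protocol article*

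**What the plan says.** The section Sample size {14} takes its inputs from a pilot of six slump and six normal-posture subjects ("Based on pilot data of 12 subjects") and fixes the error rates: "Sample size estimation was conducted according to one-tailed testing with an alpha set at 0.05 and the desired power of 0.90". For Part 1, "a sample size of 50 participants distributed in two groups was estimated", which is 25 per group under the 1:1 ratio in Trial design {8}. For the crossover: "For the second part, we calculated that 30 subjects with slump posture, are needed". Enrolment follows: "To consider a potential 20% drop-out rate, the sample size is 72 participants (36 in each group"). The effect sizes, standard deviations and the test chosen in the software are not given.

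Statistical methods {20a} plans MANOVA for slump versus normal posture, and repeated measures ANOVA with LSD post hoc comparisons for the three conditions within the slump group, with 95% confidence intervals. On the level it says only: "The significance level of tests will be considered at 0.05". The section on non-adherence and missing data {20c} makes complete cases the default and moves to an intention-to-treat analysis if more than 5% of data are missing.

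**The concern.** Two statements in the sample size paragraph do not fit the rest of the protocol.

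- **Sidedness.** The calculation puts the whole 0.05 in one tail. The MANOVA and ANOVA F tests have no direction, and LSD comparisons and 95% intervals are two-sided by convention. No section plans a directional test. For tDCS against stretching no winner is named in advance; the Introduction says the aim is to find out which is preferable.
- **Drop-out.** The 20% allowance is added by multiplying 30 by 1.2. To keep 30 after a 20% loss one divides by 0.8.

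Both errors push the true power below the stated figure in the randomised part. A reader who meets a non-significant tDCS-versus-stretching result will weigh it against a type II error of 0.10, when under the protocol's own drop-out rate it could be nearer 0.20.

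**Working it through.** **Inputs from the protocol.** One-tailed alpha 0.05, power 0.90, 25 per group (Part 1), 30 slump participants (Part 2), 20% drop-out, 36 enrolled per group (all Sample size {14}); tests at 0.05 (Statistical methods {20a}).

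**Step 1: reproduce the enrolment figure.**
- 30 × (1 + 0.20) = 36 per group, 72 in total. This matches the protocol exactly.
- Correct inflation: 30 / (1 − 0.20) = 37.5, so 38.
- Expected completers: 36 × 0.80 = 28.8, below 30.
- Loss that 36 can absorb: 1 − 30/36 = 16.7%.
- Part 1 needs 25 per group, and 28.8 exceeds 25, so this slip does not touch Part 1.

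**Step 2: back-solve the effect sizes (assumption: the base sizes came from t-tests).** The 50 and 30 cannot be reproduced without an effect size. Using the noncentral t distribution, I find the effects for which 25 per group and 30 pairs are the smallest sizes giving 0.90 at one-sided 0.05. Degrees of freedom are 2n − 2 with noncentrality d√(n/2) for Part 1, and n − 1 with noncentrality dz√n for Part 2.
- Part 1: d = 0.84 to 0.86.
- Part 2: dz = 0.55 to 0.56 (0.547 to 0.557).

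**Step 3: two-sided power at 0.05 for those effects.**

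| Part 2 completers | Power |
|---|---|
| 30 (stated requirement) | 0.83–0.84 |
| 29 | 0.81–0.83 |
| 28 | 0.80–0.81 |
| 36 (no drop-out) | 0.89–0.90 |

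| Part 1, slump / normal | Power |
|---|---|
| 25 / 25 (stated requirement) | 0.83–0.84 |
| 28 / 28 | 0.87–0.88 |
| 29 / 29 | 0.88–0.89 |
| 28 / 36 (loss in slump group only) | 0.91–0.92 |
| 36 / 36 (no drop-out) | 0.94–0.95 |

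Two-sided power of 0.90 would need 36 to 38 completers in Part 2 and 30 to 31 per group in Part 1.

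**Step 4: separate the two causes in Part 2.** One-sided power at 28 completers is 0.88–0.89, so the drop-out slip alone costs one to two points. Two-sided testing at 30 costs about seven. The sidedness mismatch carries most of the loss.

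**Step 5: the other possible origin of the 30.** If it came from a three-level, one-group repeated measures F test (sphericity assumed), set to 0.90 at n = 30, power is 0.877 at 28 and 0.889 at 29. These values do not depend on the assumed correlation between sessions, because the effect is rescaled to give 0.90 at 30. With 36 completers it is 0.95.

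**The case against.** **The size depends on inputs the protocol does not give.** This stands. The test family and effects are missing. If the software's F-test routine was used and one-tailed loosely described its upper-tail region, there is no sidedness loss and Part 2 falls short by only one to two points. The wording would then be wrong and the drop-out slip would remain, but the larger loss would not exist.

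**Part 1 might be read as equally underpowered.** The documents do not support that. The drop-out slip does not apply to it. The normal-posture group attends once, so a 20% loss there is the unfavourable case; if only the three-session slump group loses 20%, power stays above 0.90. A slump participant who leaves after the no-intervention session has still contributed to Part 1. Trial design {8} also says "the first part is exploratory research with 1:1 allocation".

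**Part 2 might be read as missing 0.90 even without drop-out.** That is not firm either: at 36 completers the range is 0.89 to 0.90, and it reaches 0.90 at the upper end of the back-solved effects.

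**Directional planning has some basis.** The abstract asks whether slump posture leads to more fatigue, and Part 2 is described as a superiority design. This could support one-sided tests of slump against normal or active against none, but none is planned, and it gives no direction for tDCS against stretching.

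**Complete cases may not be the analysis set.** At 20% loss the 5% trigger for an intention-to-treat analysis would be met. But no method for the missing sessions is given, and the switch adds no observed data, so it does not restore the planned power.

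**The drop-out error is two participants.** True, and small alone; it matters because it adds to the sidedness mismatch.

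**Conclusion.** The point holds for Part 2 and only marginally for Part 1. Two facts follow from the document without any assumption: the sizing is one-tailed while the planned tests are not directional, and 36 with 20% loss gives 28.8 completers against 30 required. The loss of power is conditional. If the base sizes came from t-tests, the crossover has about 0.80–0.83 two-sided power at 28–29 completers, so the type II error is roughly 0.17 to 0.20 where 0.10 is claimed. If the 30 came from a repeated measures F test, power there is about 0.88–0.89. For Part 1, the t-test assumption gives 0.87–0.89 in the worst case of 20% loss in both groups. The back-solved effects show the scale of the problem; they are not the pilot estimates. The stated 0.90 needs correcting, but this is no argument that the trial is too small to run.

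**What to change.** Keep 36 per group and rewrite the sample size paragraph:

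1. State the pilot effect sizes and the test used in the software for each part.
2. Recompute power from those effects for the tests planned in Statistical methods {20a}, two-sided or F, at 0.05. Do not carry over the back-solved values used here. If directional tests were really intended, specify and justify them in {20a} instead.
3. In place of the 0.90 claim, report for each part the power, or the effect detectable with 90% power, at 28–29 completers.
4. Correct the drop-out sentence: say either that 36 allows for a 16.7% loss from 36 to 30, or that about 28–29 are expected to complete Part 2 at 20% loss.

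The cost is one reworked paragraph and a short recalculation. No participants, visits or analyses change. The published power for Part 2 will probably be less favourable.

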### Recruitment {15}

Participants including students and employees of TUMS, will be recruited through online advertisements on the social media and advertising posters on bulletin boards of schools and dormitories of TUMS. Volunteers to participate in the study will be referred to the motor control laboratory at the School of Rehabilitation of TUMS. These people will be checked in terms of inclusion and exclusion criteria and a final decision will be made.

## Assignment of interventions: allocation

### Sequence generation {16a}

Randomization sequence will be generated using a web-based randomization service (https://statpages.info/latinsq.html). Given three states for slump posture group (i.e., no intervention, tDCS, and stretching exercise), there will be six different possible orders (ABC, ACB, BAC, BCA, CAB, and CBA). Each order will be performed five times in an equal ratio.

Randomization will be done at TUMS. Access to the randomization schedule will be restricted to an investigator who is not involved in the recruiting process.

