## Methods: participants, interventions, and outcomes

### Study setting {9}

The sample size is set at 36 subjects with slump posture and 36 subjects with normal posture. Participants will be recruited from TUMS (Tehran University of Medical Sciences). The present study will be conducted in the motor control laboratory at the School of Rehabilitation of TUMS. Tehran, Iran. Participants will be familiarized with the study, and they will practice with the computer. After a short break, the experiment procedures will begin.

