## Interventions

### Explanation for the choice of comparators {6b}

The normal posture group will participate just once while the slump posture group will carry out the experiment in 3 separate sessions (i.e., no intervention, stretching exercise, and tDCS) with a week interval between sessions. The sequence of sessions will be randomized. The assessor involved in analyses will be blind to groups and conditions.

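### The stated randomisation scheme defines 30 session orders (six orders, five times each), but 36 slump-posture participants are to be enrolled, so six have no defined order

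*Protocol article*

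**What the plan says.** Sequence generation {16a} takes the three states of the slump group (no intervention, tDCS, stretching), lists all six orders in which they can occur, and continues: "Each order will be performed five times in an equal ratio".

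The size of the group that needs an order is given elsewhere:

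- Study setting {9}: "The sample size is set at 36 subjects with slump posture and 36 subjects with normal posture". The Methods part of the abstract gives the same numbers.
- Sample size {14}, on the second part of the study: "we calculated that 30 subjects with slump posture, are needed". The section then applies a 20% drop-out allowance and arrives at 72 participants, 36 per group.
- Explanation for the choice of comparators {6b}: the slump group attends three sessions a week apart, and "The sequence of sessions will be randomized". The normal-posture group attends once and needs no order.

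Three further sections bear on the consequences. Sequence generation {16a} and Concealment mechanism {16b} restrict the schedule to an investigator outside recruitment and place the sequence in sealed opaque envelopes. Implementation {16c} gives screening, consent, allocation and interventions to one physiotherapist. Statistical methods {20a} compares the three conditions by repeated measures ANOVA and, as described in the article, names no period or sequence term.

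**The concern.** Every slump participant needs an order at the first session, when nobody knows who will drop out. A scheme sized to the 30 needed for analysis therefore runs out before the 36th participant arrives. The text does not say how the remaining six get an order.

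Two things are at stake. The first is concealment: the restricted schedule and the sealed envelopes protect the orders that were generated, and the protocol describes only 30. The second is balance over sessions. The protocol treats learning across sessions as a real possibility, since the Task section changes the text between sessions to counter it. With no period term named in the analysis, balanced orders are the main stated protection of the condition comparison against session effects.

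**Working it through.** **Inputs.** Orders: 6 (Sequence generation {16a}). Replicates per order: 5 (same section). Slump participants needed for the second part: 30 (Sample size {14}). Drop-out allowance: 20% (same section). Slump participants enrolled: 36 (Sample size {14}, Study setting {9}, abstract).

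**Step 1: reproduce the plan's 36.** 30 x (1 + 0.20) = 36, and 2 x 36 = 72. So 36 is the second-part requirement with the allowance added, and 30 is the figure before drop-out. The underlying 30 cannot be re-derived because no effect size is given, but this point does not depend on it.

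**Step 2: size of the scheme.** Three conditions have 3! = 6 orders. 6 orders x 5 = 30 allocations.

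**Step 3: the gap.** 36 - 30 = 6 participants without a defined order; 6/36 = 16.7%.

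**Step 4: is a balanced scheme possible for 36?** 36/6 = 6 with no remainder. Six per order covers everyone and is exactly balanced.

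**Step 5: how much could the gap matter?** The protocol does not say how the six would be filled, so only a range can be given.

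- Best case: one extra per order, giving 6:6:6:6:6:6. No imbalance.
- Simple randomisation of the six (an assumption): the chance of one per order is 6!/6^6 = 720/46,656 = 1.5%.
- Worst case: all six in one order, giving 11:5:5:5:5:5. Under simple randomisation this has probability 6/46,656 = 0.013%.

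In the worst case, let the over-used order be ABC. The number of participants having each condition at each session is then:

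| Condition | Session 1 | Session 2 | Session 3 | Mean position |
|---|---|---|---|---|
| A | 16 | 10 | 10 | 66/36 = 1.83 |
| B | 10 | 16 | 10 | 72/36 = 2.00 |
| C | 10 | 10 | 16 | 78/36 = 2.17 |

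Full balance would give 12 in every cell. For additive session effects p1, p2, p3, the A minus C contrast picks up (16 - 10)/36 x (p1 - p3), which is one sixth of the difference between the first and third sessions. If the effect is linear, that difference is two session steps, so the contrast shifts by 2/6 = one third of a step. This agrees with the difference in mean position, 12/36 = 0.33.

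**The case against.** The best defence is that the sentence describes completed sequences: five completers per order makes the 30 needed, and the other six are the drop-out allowance. The wording permits this, and the article never says that only 30 envelopes exist. But the sentence stands under sequence generation, orders are handed out before drop-out is known, and no rule lets a later participant take over a drop-out's order. A replacement rule could sit in a fuller protocol. Even so, the article states an allocation count, and that count does not fit its own sample size. This is a figure to be reconciled, not a detail left out.

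The other objections limit how far the point goes, and they are right.

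- A reader might infer that the orders will be unbalanced. The documents do not support that. The 30 stated allocations are balanced, and the other six could be filled evenly. Imbalance is a risk only.
- A reader might infer that the enrolling physiotherapist could know or choose the order for the last six. No section describes ad hoc ordering or reuse of envelopes. Schedule access is restricted and envelopes are specified. That the physiotherapist carries out allocation does not show access to the schedule.
- A reader might infer that protection against session effects is lost. Every participant receives all three conditions, and the worst case above weakens balance only modestly.
- Drop-outs may fall unevenly over the orders, but this applies to any crossover trial, including one with six per order. It is no argument against this sentence.

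**Conclusion.** The mismatch is real: the stated scheme yields 30 orders for 36 people who each need one. Six participants (16.7% of the crossover sample) have no defined order, and concealed, balanced allocation is not assured for them. This rests only on counts in the protocol and on reading the sentence as a statement about allocation, which is where it is placed.

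The likely effect on results is small. The bound of one third of a linear per-session effect assumes additive session effects, all six extra participants in a single order, and no period term in the analysis. The stated sample sizes and outcomes are untouched. The sentence should be corrected, but the error does not by itself undermine the trial.

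**What to change.** In Sequence generation {16a}, state that each of the six orders is allocated six times (6 x 6 = 36), and that the list is generated in advance for all 36 slump participants under the same restricted access and sealed envelopes. If 30 completers were meant, say so and state how every enrolled participant, including the six beyond 30, receives an order.

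The Trial status section expected recruitment to finish on 5 February 2023, before publication on 24 May 2023, so the list may no longer be open to change. In that case the sponsor should state how participants 31 to 36 received their order and report the realised number of participants per order.

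The cost is one sentence and six more envelopes, or, after enrolment, a short statement and a table of six counts. The sample size does not change.

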### Concealment mechanism {16b}

The random allocation sequence is printed onto papers which will be then sealed in opaque envelopes.

### Implementation {16c}

Enrolment including eligibility screening, informed consent, and allocation, interventions will be conducted by a physiotherapist who is not involved in the analysis of data.

## Assignment of interventions: blinding

### Who will be blinded {17a}

This is a single-blind study. The assessor who analyses the outcomes and performs the statistical analyses will be blind to groups and conditions and will not participate in taking measurements.

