#### Task

Previous research showed that working with a computer for a period of 45 to 60 min had reduced the performance to its minimum level [26]. So, in this study, 60 min are considered for typing, and spell-check of the word program will be turned off for all conditions. Three different Persian texts from a single book are selected for the study. The same text will be used for individuals with normal and slump posture (i.e., no intervention). But for the intervention sessions, the text will be changed to prevent the learning effect.

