### Data management {19}

At the beginning of the study, participants will be assigned a unique identification code and the data sent to the study assessor will only include the code without participant identification information. Subjective assessments and demographic information collected on paper forms will be entered into specific Excel files and a second study staff member will check the data entry process for accuracy. All paper-based data for the study including consent forms, identifiable information, and questionnaires will be kept separate from each other in a locked cabinet in the motor control laboratory at the School of Rehabilitation of TUMS. The electronic records of the study, i.e., raw data of EEG, Entropy, and the Excel files stored on a password-protected external hard drive and computer. Both paper and digital documents will only be accessible to the research team.

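### The assessor's blind to group and to untreated versus treated sessions is claimed without qualification, but the described coding, session counts and typing texts do not deliver it

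*Protocol article*

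**What the plan says.** The article describes the study as assessor-blinded (Trial design {8}). Two sections state the scope of the blind. Explanation for the choice of comparators {6b} says "The assessor involved in analyses will be blind to groups and conditions". Who will be blinded {17a} says "The assessor who analyses the outcomes and performs the statistical analyses will be blind to groups and conditions", so one person both scores outcomes and runs the statistics; that section also keeps this person out of the measurements. Procedure for unblinding {17b} treats the trial as otherwise open-label, so this is the only blinding in the study.

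The procedures that bear on the claim are these:

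- **Coding.** Under Data management {19}, "participants will be assigned a unique identification code". The section goes on to say that "the data sent to the study assessor will only include the code without participant identification information". No session-level code is described.
- **Sessions.** "The normal posture group will participate just once while the slump posture group will carry out the experiment in 3 separate sessions" (section {6b} again).
- **Texts.** Under Task, "Three different Persian texts from a single book are selected for the study". One text serves the normal group and the slump no-intervention session. "But for the intervention sessions, the text will be changed to prevent the learning effect".
- **Typing scores.** Under Outcomes {12}, Task performance, the assessor calculates typing speed and errors.
- **Analysis.** Statistical methods {20a} plans a repeated measures ANOVA over the three conditions, in the slump group only.

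**The concern.** A participant-level code removes names. It does not remove the structure of the data, and here that structure differs by group. The typing material differs between untreated and treated sessions as well, and the person who should be blind works with it.

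This matters because the expected direction of each comparison is plain: slump worse than normal, treated better than untreated. If scoring involves any judgement, for example in counting errors or tracking video markers, knowledge of group or treatment could shift the scores that way. Readers of the eventual report would meanwhile judge detection bias on an unqualified statement that the assessor was blind to both group and condition.

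**Working it through.** The plan gives no figure to reproduce here. The check is to count what the assessor can infer from the material described.

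**Inputs**
- Planned participants: 36 slump and 36 normal (Study setting {9}).
- Sessions per participant: 3 slump, 1 normal (Explanation for the choice of comparators {6b}).
- Codes: one per participant (Data management {19}).
- Possible session orders: 6 (Sequence generation {16a}).
- Texts: 3, one of them shared by the normal group and the slump no-intervention session (Task).

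**Step 1: group, from the number of records**
- Slump records: 36 × 3 = 108.
- Normal records: 36 × 1 = 36.
- Total: 108 + 36 = 144 records under 72 codes.

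A code with three records must be slump. A code with one record is normal, unless it belongs to a slump participant who left after the first session. With complete data the count separates all 72 participants.

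**Step 2: group, at the analysis stage**

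The repeated measures ANOVA needs each slump participant's three sessions linked. Whoever runs it sees which participants have three sessions, whatever labels are used. The same person scores the outcomes, and the article states no lock of the scores before linkage.

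**Step 3: condition, from the typed text**

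Write N for no intervention, T for tDCS and S for stretching. The six orders are NTS, NST, TNS, SNT, TSN and STN. The session with the shared text is N. Once its position is known, two orders remain:
- N first: NTS or NST.
- N second: TNS or SNT.
- N third: TSN or STN.

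The chance of guessing the full order rises from 1/6 to 1/2. The untreated session itself is identified with certainty for each of the 36 planned slump participants. The order of T and S stays at 1/2, because the article does not tie either of the other two texts to an intervention.

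**Step 4: which outcomes each route reaches**
- Typing speed and errors: record count and text.
- EEG band power (primary outcome): record count only. Its derivation under Electroencephalography uses no typed text.
- Video-derived neck measures: record count, plus a visual cue. The typing video yields the craniovertebral angle, which is one of the two angles that define the groups (Eligibility criteria {10}).

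**The case against.** **File naming may be settled elsewhere.** The article does not say how a slump participant's three files are named or whether they reach the assessor together, and a condensed article may leave that to a fuller document. This stands in part: at the scoring stage, the record-count route assumes that files arrive under the participant code, which is the only mechanism described. It does not answer the analysis stage, where linkage is unavoidable, or the text route.

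**Other safeguards exist.** The assessor takes no measurements, a separate investigator collects data, the physiotherapist who enrols and treats is kept out of the analysis, and access to the schedule is restricted. These are real protections and limit other leaks. None closes the two routes above.

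**Scoring may leave little room for judgement.** EEG power comes from software, typing outcomes are counts per minute, and the article does not say that errors are counted by eye or that the assessor rejects EEG artefacts by hand. This stands as a limit on consequence: bias is possible, but it is not shown.

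**Stronger readings.** A reader might infer that the whole blind fails, including tDCS versus stretching. The documents do not support that, since nothing described shows which intervention was given. A reader might also infer that the text unmasks the EEG outcome, but no text enters its derivation. Finally, a reader might take the typing video as proof of group. Group also depends on the thoracic kyphosis angle, both angles are classified from a separate baseline photograph, and the video has no T12 marker. The video is a cue only.

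**Conclusion.** The point holds in a limited form. The article claims blindness to groups and conditions without qualification, while its own procedures leave group readable from the record count for complete participants and visible in the statistical analysis. They also leave the untreated session identifiable when typing is scored. The contrasts exposed are normal versus slump and untreated versus treated. The tDCS-versus-stretching contrast is not shown to be exposed.

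The conclusion rests on two assumptions: that files reach the assessor under the participant code as described, and that calculating typing errors means working with the typed text or its source. The counts of 72 and 36 are planned numbers and apply to participants with complete data. The size of any bias cannot be calculated from the document.

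**What to change.** 1. **Who will be blinded {17a} and Data management {19}:** send every recording to the assessor under a random session-level code, 36 + 3 × 36 = 144 planned. The key is held by the investigator who has the randomisation schedule, who must not be the assessor. Link sessions to participant and condition only after all EEG, kinematic and typing scores are locked.
2. **Task performance:** score typing by a scripted comparison with the source text, so that the assessor does not see which text was used.
3. **Trial design {8}, Explanation for the choice of comparators {6b} and Who will be blinded {17a}:** restate the claim. Scoring is masked to session. The statistical analysis is masked at most to tDCS versus stretching, under neutral labels. Group is not masked in the statistical analysis and may not be masked for video-derived measures.

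Neutral labels alone would not be enough, because the arm with one record per participant would still be recognisable as the normal group.

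The cost is a file-naming rule, a short text-comparison script and changes of wording, with no extra visits or procedures. If scoring is already complete, the third change can still be made, so that the report claims only the masking that was in place.
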